### Control group

Similarly, at the end of each dialysis session, the “control” patient will be asked to estimate his pain level, boredom level and mood perceived during the session, with a visual analogue scale graduated from 0 to 10 [38].

### Outcome measures

All the measures listed below will be assessed at the baseline t_*0*_, and during the eighth week (t_+2_), the sixteenth week (t_+4_) and the twenty-fourth week (t_+6_) of the 6-month adapted rehabilitation program.

### Primary outcome measures

The primary outcome of this study is the number of patients who are no longer in a state of protein energy wasting after 6 months of exercise training compared to the control group. We define correction of PEW as the normalization of albumin and prealbumine, and of the lean tissue index, considering these items to be the clinically most relevant for the diagnostic criteria of PEW.

#### Biological sample

Patients in both groups will have routine serum chemistry measures according to follow-up guidelines for dialysis patients in terms of serum electrolytes, -bicarbonate, s-urea and creatinine, urea reduction rate, KT/V monthly, PTH and 25 OH vitamine D, which will be measured at the beginning and at the end of the study. Patients will receive oral native vitamin D supplementation in order to maintain serum 25 OH levels in the normal laboratory range.

#### Dietetics survey

Protein and energy intake will be assessed by a qualified dietitian by means of a 3 day food record at the beginning and at the end of the study.

### Secondary outcome measures

Secondary outcome measures include: (i) changes in biological markers of nutrition (albumin and prealbumine), body composition (LTI, FTI), muscle strength, walk function, postural stability, quality of life, days of hospitalization, and survival.

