**Methods and design:**

Fifty end-stage renal disease patients undergoing hemodialysis, who meet the diagnostic criteria for PEW, will be randomly allocated into an *exercise* or *control* group for 6 months. The exercise consists of a progressive submaximal individualized cycling exertion using an adapted cycle ergometer, during the three weekly dialysis sessions. Biological markers of nutrition (albumin, prealbumin) will be followed monthly and all patients will be assessed for body composition, walk function, muscle strength, postural stability and quality of life at baseline and during the eighth week (t_+2_), the sixteenth week (t_+4_) and the twenty-fourth week (t_+6_) of the 6-month adapted rehabilitation program.

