### Statistical analysis

The sample size was calculated considering the number of patients who are no longer in a state of protein energy wasting after 6 months of exercise training compared to the control group. For a significance level of 0.05 and 80% power, it was estimated that 22 participants would be required in each group.

Results will be expressed as minimum to maximum or percentage of change, as applicable, and mean ± standard deviation. To test the effects of Group (Exercise *versus* Control) on all outcome measures, univariate two-way analyses of variance (ANOVAs), with the Group (×2) as between-subjects factor and Time (t_0_, t_+2_, t_+4_ and t_+6_) as the within subject factor, will be carried out for each aforesaid dependent variable. For each analysis, the level of significance was p < 0.05. Newman-Keuls comparisons will be used for post-hoc tests following significant effects. If the sphericity assumption in ANOVA is violated (Mauchly’s test), corrected tests of significance will be used [45,46]. In that case, the paired t-tests with corrected alpha level will be used as post-hoc comparisons. All the statistical analyses will be conducted using a SPSS software package.

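### The Group × Time ANOVA prescribed for every outcome suits neither survival nor days of hospitalisation

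*Protocol article*

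**What the plan says.** Under Secondary outcome measures, the Protocol article closes its list with "quality of life, days of hospitalization, and survival". The other secondary outcomes each get a subsection saying how they are measured. These two do not.

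The general lead-in under Outcome measures reads "All the measures listed below will be assessed at the baseline" and continues with weeks 8, 16 and 24 of the programme. No later text sets a different schedule for hospital days or survival.

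Under Statistical analysis, the effect of group is to be tested "on all outcome measures, univariate two-way analyses of variance (ANOVAs". Group is the between-subjects factor, and Time, with levels t0, t+2, t+4 and t+6, enters "as the within subject factor, will be carried out for each aforesaid dependent variable". No other method of comparing the groups is named for any outcome.

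**The concern.** Survival is a time-to-event outcome, and hospital days accrue over a period that differs between patients. A four-level repeated-measures ANOVA has no term for time observed, censoring or death. Applied as written, it gives an answer for these two outcomes that does not reflect what happened to patients who died, were transplanted, transferred or withdrew.

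This matters because these are the only hard clinical outcomes in the secondary list. The article's own Abstract describes protein-energy wasting as a strong predictor of morbidity and mortality, so early deaths and exits are foreseeable. The trial is open-label and only one arm cycles, so exits may also differ between arms. A comparison of hospital days that mishandles early exits could then understate the burden in the arm that loses more patients.

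**Working it through.** **Plan's own figure.** The article gives no design figure for either outcome. Its only one, 22 per group, belongs to the primary outcome. The two correction rates behind it are not stated, so it can only be back-solved (for example 10% against 48%, two-sided, without continuity correction). It has no bearing here.

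**Survival under the stated method.** At t0 every patient is alive, so the outcome has no variation at that level of Time. Two readings follow.
- If only patients with all four assessments enter, as is usual in a conventional repeated-measures ANOVA, all of them are alive throughout and there is nothing to compare.
- If death is scored at later visits, the date of death is lost and a patient with unknown status has no valid value.

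**Hospital days under the stated method.** The article does not say how early exits are handled, so both possibilities are worked through.

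Inputs:
- Follow-up T = 6 months (Protocol article, abstract, Methods and design).
- Assumptions, not from the article: survivors have the same hospital-day rate in both arms; deaths occur in one arm only, in a proportion m of its patients, on average at month 3; patients who die have k times the survivors' rate while alive.

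Formulas, as arm with deaths over the other arm, with the survivors' rate set to 1 per month:
- Raw mean days ratio = [6(1 − m) + 3mk] / 6.
- Rate ratio per time at risk = [6(1 − m) + 3mk] / [6(1 − m) + 3m].
- Completers-only ratio = 6/6 = 1.00.

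| m | k | Raw ratio | Rate ratio | Completers only |
|---|---|---|---|---|
| 5% | 1 | 0.975 | 1.00 | 1.00 |
| 10% | 1 | 0.95 | 1.00 | 1.00 |
| 10% | 2 | 1.00 | 1.05 | 1.00 |
| 10% | 3 | 1.05 | 1.11 | 1.00 |
| 10% | 5 | 1.15 | 1.21 | 1.00 |
| 20% | 1 | 0.90 | 1.00 | 1.00 |
| 20% | 2 | 1.00 | 1.11 | 1.00 |
| 20% | 3 | 1.10 | 1.22 | 1.00 |
| 20% | 5 | 1.30 | 1.44 | 1.00 |

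Worked line: m = 20%, k = 5 gives (4.8 + 3.0)/6 = 1.30 raw and 7.8/(4.8 + 0.6) = 1.44 as a rate.

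Dividing the first formula by the second gives raw ratio / rate ratio = 1 − m/2, whatever k is. That is 0.95 at m = 10% and 0.90 at m = 20%. So raw days understate the rate ratio by 5% and 10%. The completers-only analysis understates it whenever patients who die had a higher rate than survivors.

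**Direction of the raw comparison.** With death at month 3, raw totals are equal at k = 2 and the arm with deaths looks worse above that. The break-even depends on when patients leave. Take an invented patient who dies at week 6 (42 days) with 10 hospital days and another who completes 24 weeks (168 days) with 12. The rates are 10/42 = 23.8% and 12/168 = 7.1%, a ratio of 3.3, yet the raw total is lower in the patient who died. Break-even is 168/42 = 4 times the rate. With 13 days instead of 10, the raw order reverses.

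**The case against.** The strongest defence is that a journal article condenses the full protocol. Exposure time, censoring and follow-up after withdrawal are commonly left to that document or to the analysis plan, and neither is shown. The lead-in under Outcome measures is also loose: the article itself departs from it for PTH and vitamin D, for the food record, and for monthly albumin and prealbumin. Collecting events at visits is no fault in itself, since admissions and deaths can be recorded back to the previous visit. A patient who merely stops cycling may well still be dialysed, and so observed, at the unit.

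Much of this stands, and it rules out several stronger readings.
- A reader might infer that hospital days are simply totalled, or that deaths after leaving go uncounted. The article says neither; both would be inferences from silence.
- A reader might infer that an early death makes its arm look better. The working shows that this depends on the hospital-day rate before death and on its timing. A conventional repeated-measures ANOVA would usually drop such a patient rather than credit the arm with few days.
- A reader might infer that a few such patients would reverse the comparison. Three patients differing by 2 days each, in an arm of 25 (half of about 50), shift its mean by 6/25 = 0.24 days. That matters only if the arms are already nearly equal.

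The defence does not cover the method. On the analysis the article is not silent: it names one technique for every outcome, and that technique does not suit these two.

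**Conclusion.** The point holds as a minor one. The Statistical analysis section, read with the two outcome sections, assigns survival and hospital days to an ANOVA that cannot use death or censoring times and takes no account of unequal time at risk. The size of the effect rests on the stated assumptions: deaths in one arm only, mean time of death at month 3, and equal rates among survivors. On those terms, raw days understate the rate ratio by 5% at 10% mortality and 10% at 20%, and completers-only results can hide it altogether. The article gives no mortality or hospital-day figures, so the actual size is unknown. Both outcomes are secondary in a trial of about 50 patients, and neither the sample size nor the primary conclusion depends on them.

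**What to change.** - State in the Statistical analysis section that the Group × Time ANOVA does not apply to survival or days of hospitalisation.
- For every randomised patient, including those who stop cycling or leave the programme, record dates of death, transplant, transfer and each admission from unit records, from randomisation to week 24, where consent allows.
- Analyse survival as time from randomisation to death, censored at week 24 or when last known alive.
- Report hospital days per patient-day at risk by arm, for example from a count model with a follow-up offset, with deaths by arm shown alongside. The deaths are needed because a rate alone does not show that follow-up ended in death.

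The cost is small: a change of wording, dates taken from existing records, and one status check at week 24 for patients who have left. With about 25 patients per arm the estimates will be imprecise whichever method is used.

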#### Biological markers of nutrition (albumin and prealbumine)

Serum albumine and -prealbumine will be measured monthly. BMI will be calculated at month t_+2_, t_+4_ and t_+6_. Serum albumine is measured by the bromcresol green method (normal range (38–52 g/l), serum prealbumine is measured by the immune-turbidimetric method (normal range 300–400 mg/l).

#### Body composition

Body-composition (overhydration, lean tissue index (LTI, kg/m^2^) and fat tissue index (FTI, kg/m^2^) will be measured by bioimpedance spectroscopy using a Body Composition Monitor (BCM, Fresenius Medical Care, Bad Homburg, Germany) at month 2, 4 and 6 just before the midweek dialysis session.

#### Walk function

The walk function assessment will be performed using a 6 min-walk-test (6MWT). This test has been considered to be an appropriate test to assess a patient’s functional and physiological response and cardiovascular fitness [39]. Patients will walk along a measured circuit (15 m), and are instructed to cover as much distance as possible in the six minutes. Blood pressure, heart rate and rating perceived exertion (RPE) will be assessed before and after the 6MWT.

#### Muscle strength

Maximal quadriceps strength during a knee extension will be tested using a manual dynamometer (Metil Industry©, Belgium). Patients will perform three maximal leg extensions in sitting position before a dialysis session. At least five minutes of recovery will be provided between 2 consecutive measurements.

#### Quality of life

The self-reported quality of life will be evaluated using the Medical Outcome Study Short Form 36 (SF-36) [40-42], which has been documented to be reliable and valid in dialysis patients [10,43]. This SF-36 is a generic multidimensional instrument consisting of eight multi-item scales representing: (1) physical functioning (extent to which health limits physical activities, such as self-care, walking, and climbing stairs), (2) social functioning (extent to which physical health or emotional problems interfere with normal social activities), (3) role-functioning physical (extent to which physical health interferes with work or other dally activities), (4) role-functioning emotional (extent to which emotional problems interfere with work or other daily activities), (5) mental health (general mental health, including depression, anxiety, behavioral and emotional control, and general positive effect), (6) vitality (feeling energetic and full of pep rather than tired and worn out), (7) bodily pain (intensity of pain and effect of pain on normal work, both inside and outside the home), and (8) general health perceptions (personal evaluations of current health, health outlook, and resistance to illness).

#### Postural stability

Balance during a quiet stance will be tested after a rest period before the dialysis session. The postural test will consist of two conditions of quiet stance: stance on a firm surface with eyes open (EO) and stance on a firm surface with eyes closed (EC). Participants will stand quietly while barefoot, with the head in a straight-ahead position, their arms along the body. During conditions with eyes open, they will be instructed to look at a black spot (with a diameter 2 cm diameter) placed on a white wall in the front of them at a 2 m distance. For each condition, two trials will be performed. The duration of each trial will be 60 s followed by a rest period of 1 minute. During thee condition with EO, the subject’s eyes will focus on a stationary eye-level visual target (a black spot with a 2 cm diameter) situated at a 2 m distance. For all data collection of postural sway, we will use a Kistler force plateform (model 9286BA) with subject weight normalization. Data will be sampled at 100 Hz and recorded online. The body sway will be quantified by displacement of the center of foot pressure (COP) in the anterior-posterior (AP) and in the medial-lateral direction (ML). For measuring all of the COP parameters, raw data will be filtered using a fourth-order Butterworth, zero-phase low-pass at 10 Hz. The COP parameters will then be the mean and standard deviation (SD) of COP position in AP and ML directions, SD of velocity in AP and ML directions, mean velocity and area (90% confidence ellipse) (see [44] for details of formulas).

### Statistical analysis

The sample size was calculated considering the number of patients who are no longer in a state of protein energy wasting after 6 months of exercise training compared to the control group. For a significance level of 0.05 and 80% power, it was estimated that 22 participants would be required in each group.

Results will be expressed as minimum to maximum or percentage of change, as applicable, and mean ± standard deviation. To test the effects of Group (Exercise *versus* Control) on all outcome measures, univariate two-way analyses of variance (ANOVAs), with the Group (×2) as between-subjects factor and Time (t_0_, t_+2_, t_+4_ and t_+6_) as the within subject factor, will be carried out for each aforesaid dependent variable. For each analysis, the level of significance was p < 0.05. Newman-Keuls comparisons will be used for post-hoc tests following significant effects. If the sphericity assumption in ANOVA is violated (Mauchly’s test), corrected tests of significance will be used [45,46]. In that case, the paired t-tests with corrected alpha level will be used as post-hoc comparisons. All the statistical analyses will be conducted using a SPSS software package.

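### The yes/no primary outcome at 6 months is assigned to a Group × Time ANOVA over four visits, and neither of its Group terms tests the 6-month difference in proportions

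*Protocol article*

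**What the plan says.** The article's Primary outcome measures section states: "The primary outcome of this study is the number of patients who are no longer in a state of protein energy wasting after 6 months". The comparison is exercise against control. The same section makes this a status for each patient: "We define correction of PEW as the normalization of albumin and prealbumine, and of the lean tissue index". The primary outcome is therefore yes or no, read at one time point.

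The Statistical analysis section bases the sample size on that same count (22 per group, significance level 0.05, 80% power). It then sets out one method for testing Group effects: "on all outcome measures, univariate two-way analyses of variance (ANOVAs"). Group is the between-subjects factor, and Time (t0, t+2, t+4, t+6) enters "as the within subject factor". These analyses "will be carried out for each aforesaid dependent variable". Post-hoc comparisons are Newman-Keuls after a significant effect, or paired t-tests with a corrected alpha if sphericity fails.

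No comparison of proportions is named and the primary outcome is not exempted. The Secondary outcome measures section also lists "quality of life, days of hospitalization, and survival", so the last two of these fall under the same rule.

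**The concern.** The question, the sample size and the test should refer to the same quantity. The first two do: the proportion corrected at 6 months. The prescribed test does not. A two-way ANOVA with four visits offers a Group effect and a Group × Time effect. The first concerns the average over visits, the second the shape of the profile. The article does not say which one decides the trial.

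At stake is the meaning of a significant result. Followed as written, the trial could be declared positive on a difference that has gone by month 6. A true month-6 difference would be judged by a quantity that depends on how early it appeared. With two candidate terms and no rule, the choice could also be made after the data are seen.

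**Working it through.** **1. The stated sample size.** The article gives no control rate, exercise rate or difference, so 22 per group cannot be reproduced as a unique figure. For a two-sided comparison of two proportions without continuity correction,

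n = [1.96·√(2·p̄·(1−p̄)) + 0.8416·√(p₁(1−p₁) + p₂(1−p₂))]² / (p₂−p₁)².

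With assumed rates of 20% and 61%, p̄ = 0.405 and n = (1.361 + 0.531)² / 0.41² = 3.578 / 0.1681 = 21.3, so 22. Other pairs give 22 as well, such as 5% vs 40%, 10% vs 48% or 30% vs 72%. The stated figure is thus compatible with a test of 6-month proportions.

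**2. The outcome at t0.** The Inclusion criteria require at least three of four categories: serum chemistry, body mass, muscle mass, dietary intake. At most one category can be unmet, so every patient has an abnormal serum or muscle category. Correction requires normal albumin, prealbumin and lean tissue index. If lean body mass (entry) and lean tissue index (outcome) are taken as equivalent, nobody is corrected at t0. The variable is 0 for all patients in both arms, with zero variance at that visit.

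**3. What the Group effect estimates.** It is the mean difference over four visits, one of which is fixed at zero. For 20% vs 60% at t+6:
- benefit only at t+6: (0 + 0 + 0 + 40)/4 = 10 points;
- 10 points at t+4, then 40: (0 + 0 + 10 + 40)/4 = 12.5 points;
- linear onset: (0 + 13.3 + 26.7 + 40)/4 = 20 points.

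With 40% in both arms at t+6 but 10% vs 40% at t+2 and t+4, it is (0 + 30 + 30 + 0)/4 = 15 points, although the 6-month difference is zero.

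**4. What Group × Time tests.** It has (2−1)(4−1) = 3 degrees of freedom and responds to any departure from parallel profiles.

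**5. Simulation.** Inputs: 22 per arm (article); latent normal correlation of 0.6 between visits (assumption); corrected rate 0 at t0 (step 2); visit rates as shown (assumptions). The entries are the percentage of trials with p < 0.05. The direct test is a chi-square on t+6 proportions.

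| Scenario | Group | Group × Time (uncorrected) | Direct test at t+6 |
|---|---|---|---|
| 20% vs 60% at t+6, late benefit | about 48–58 | 84–87 | 79 |
| 20% vs 60% at t+6, linear onset | about 81 | 73 | 79 |
| 40% vs 40% at t+6, 10% vs 40% earlier | about 49 | 71 | 5 |

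Other assumed rates give the same pattern. For 20% vs 61% at t+6, Group reaches 46% if the effect appears only at t+6, 83% with linear build-up and 96% if it is present from t+2. The direct test stays at 80–81% throughout. For equal 30% rates at t+6 with 10% vs 45% earlier, Group rejects in 64% and Group × Time in 87% (85% after Greenhouse-Geisser correction), against 4.5% for the direct test.

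Under a full null (equal rates at every visit), Group rejects in 5.4–6.2% of trials and Group × Time in 6.6%, or 4.9% after correction.

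**The case against.** The best defence is that the ANOVA wording was written for the continuous measures. Means with standard deviations and the sphericity test suit those, the sample-size sentence already treats the primary outcome as a count, and a fuller document may name a test of proportions. This lowers certainty about what the investigators intend. It does not remove the fault: the article is not silent on the method but prescribes one for all outcomes, and a later plan naming another test would contradict it.

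A second defence is that Group × Time, not Group, usually carries the treatment effect when arms share a baseline. This has force. A reader might infer from the 48–58% that the planned analysis would miss a late benefit. The calculations do not support that, because Group × Time reaches 84–87% in the same scenarios, above the direct test. Its only shortfall here is modest (73% vs 79%, linear onset). Yet the interaction also rejects more often than Group when the 6-month proportions are equal, so choosing it does not restore the 6-month question.

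A third defence is the post-hoc step. Newman-Keuls could compare the arms at t+6, but only after a significant overall effect and as a comparison of means. The fallback paired t-tests are within-patient and do not compare arms.

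Survival and hospital days appear only in a list of secondary outcomes. They show how wide the wording is but add little weight.

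**Conclusion.** The mismatch stands and is wrong as written. The primary outcome is a 6-month yes/no status, while the assigned analysis tests a four-visit average or a 3-df profile difference. A 40-point difference at t+6 enters the Group effect as about 10–20 points. Equal 6-month rates after an earlier difference give significance in about 49% (Group) or 71% (Group × Time) of simulated trials.

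A reader might take those last figures as type I error inflation. They are not: the arms truly differ at earlier visits, so the ANOVA null is false, and under a full null its error is near nominal. The fault is the hypothesis tested.

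The dilution follows from arithmetic once t0 is zero, which needs lean body mass and lean tissue index to be equivalent. The rejection rates also rest on assumed visit rates and on the correlation of 0.6, and would shift with other values. The contradiction between the two sections needs none of these assumptions.

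**What to change.** In the Statistical analysis section, state that the primary analysis compares the proportion of patients with PEW corrected at t+6 between exercise and control, using a two-proportion test (for example chi-square or an exact test), reported as a risk difference with a 95% confidence interval. Restrict the repeated-measures ANOVA to the continuous outcomes measured at the four visits, and exclude survival and days of hospitalization from it.

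The cost is a sentence or two of wording, with no new data and no change to the stated 22 per group. The choice among standard tests and intervals, and the handling of missing 6-month assessments, are separate matters that this fault does not settle.

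### For continuous outcomes the repeated-measures ANOVA counts baseline as an outcome visit, names no 6-month treatment contrast and drops any patient with a missed visit

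*Protocol article*

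**What the plan says.** The Statistical analysis section of the protocol article opens its analysis plan with the aim "To test the effects of Group" on all outcome measures. The method is a univariate two-way ANOVA with Group between subjects and Time, at t0, t+2, t+4 and t+6, "as the within subject factor, will be carried out for each aforesaid dependent variable". Baseline is therefore a level of the response and not a covariate.

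On sphericity the section says: "If the sphericity assumption in ANOVA is violated (Mauchly’s test), corrected tests of significance will be used". In that case the post-hoc comparisons are paired t-tests at a corrected alpha; otherwise Newman-Keuls comparisons follow significant effects. The threshold is stated once for all: "For each analysis, the level of significance was p < 0.05". On software: "All the statistical analyses will be conducted using a SPSS software package". Together these describe the classical repeated-measures ANOVA.

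The section does not say which term of the model (Group or Group x Time) is the treatment test, and it names no between-group contrast at t+6.

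**The concern.** Randomised arms have an expected difference of zero at t0. A Group main effect over four visits averages that zero with the three follow-up differences, so it understates the effect of treatment. The early visits may dilute it further. Under Exercise group, the cycling time rises from 10 minutes in month 1 to 15 in month 2, 20 in months 3-4 and 30 in months 5-6, so an effect that grows towards t+6 is plausible. The primary outcome is also set at 6 months.

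The same ANOVA does yield a Group x Time test that is not diluted in this way. It is an omnibus test on 3 df, however, and gives no estimate or confidence interval at 6 months. The paired t-tests prescribed when sphericity fails compare visits within patients, not exercise with control. With two candidate tests, each at 0.05, the choice between them could follow the data.

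Finally, this form of ANOVA needs a value at every level of Time. Hospital days and survival are listed as secondary outcomes, so the trial itself foresees events that can prevent a visit.

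**Working it through.** **The plan's own figure.** "For a significance level of 0.05 and 80% power, it was estimated that 22 participants would be required in each group" That number was computed for the binary primary outcome, and the article gives no response rates, so it can be neither confirmed nor refuted. Many pairs give 22 per group (two-sided, no continuity correction: 10% against 48%, or 20% against 61%). The point does not depend on it; 22 per arm serves below only as a working size.

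**Inputs.**
- From the article: four visits; 22 per arm; alpha 0.05 (taken as two-sided); about 50 patients recruited.
- Assumed, because the article gives no such values: SD 1, effect of 0.8 SD at t+6, equal correlation r between visits of 0.4 to 0.8, and independent missed visits at a rate of 5-10%.

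**Dilution (no SD or correlation needed).**
- Constant follow-up effect d: (0 + d + d + d)/4 = 3d/4. With d = 0.8 this is 0.60 SD.
- Linear growth to d at t+6: (0 + d/3 + 2d/3 + d)/4 = d/2. With d = 0.8 this is 0.40 SD.

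**Power formulas, n = 22 per arm.**
- Group main effect: SE = sqrt[(2/n)(1 + 3r)/4], noncentral t on 42 df.
- Group x Time: noncentrality = (n/2) x S/(1 - r), where S is the sum of squared deviations of the four visit effects from their mean; F on 3 and 126 df. S = 0.48 (constant) or 0.356 (linear).
- Baseline-adjusted ANCOVA at t+6: SE = sqrt[(2/n)(1 - r²)], noncentral t on 42 df, treating the baseline slope as known.

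**Example, linear effect, r = 0.6.**
- Group: SE = sqrt(0.0909 x 0.70) = 0.252; 0.40/0.252 = 1.59; power 34%.
- Interaction: 11 x 0.356/0.4 = 9.8; power 74%.
- ANCOVA at t+6: SE = sqrt(0.0909 x 0.64) = 0.241; 0.80/0.241 = 3.32; power 90%.

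| r | Group, linear | Group x Time, linear | Group, constant | Group x Time, constant | ANCOVA at t+6 (either profile) |
|---|---|---|---|---|---|
| 0.4 | 42% | 54% | 75% | 69% | 81% |
| 0.5 | 37% | 63% | 69% | 77% | 85% |
| 0.6 | 34% | 74% | 64% | 87% | 90% |
| 0.7 | 31% | 86% | 60% | 95% | 95% |
| 0.8 | 29% | 97% | 56% | 99% | 99% |

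Simulation of the linear case (4,000 trials per setting) agrees: at r = 0.4 / 0.6 / 0.8, Group 42 / 34 / 30%, interaction 54 / 73 / 97%, ANCOVA 80 / 89 / 99%.

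**Complete cases.** With three follow-up visits missed independently at rate p, the expected number complete is 50 x (1 - p)³.
- p = 5%: 50 x 0.857 = 42.9.
- p = 10%: 50 x 0.729 = 36.5.
- If instead the same 10% of patients miss every follow-up visit: 50 x 0.90 = 45.

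**The case against.** The strongest reply is that the dilution depends on reading the treatment test as the Group main effect alone. A Group by Time ANOVA also produces Group x Time. Mauchly's test concerns only the within-subject terms, and post-hoc comparisons serve no purpose for a main effect with two levels. Both suggest that the authors expect to read the interaction. This stands: dilution is a consequence of one reading and not a settled fact, and on the other reading the power loss is much smaller. What remains is that the text does not choose, and that the interaction gives no 6-month estimate.

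A reader might infer several stronger things that the document does not support.
- **That the reported effect will be half the true one.** This holds only for linear growth; for a constant effect the factor is 3/4.
- **That every secondary outcome loses power.** Hospital days and survival are secondary outcomes but are not measured as continuous values at four visits.
- **That complete cases fall below a required 44 (2 x 22).** That number was sized for the binary primary outcome; the article states no requirement for the continuous ones.
- **That the dropped patients would be mainly the hospitalised, the transplanted or the dead.** The article gives no dropout rates or reasons and does not mention transplantation.

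The article also leaves missing-data handling unstated, as articles commonly do, and a fuller plan could add imputation or a mixed model. That silence is not the finding. The finding is that the method named here works only on patients with all four visits. Several measurements are tied to dialysis sessions that patients attend anyway, so the missed-visit rate may be low.

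**Conclusion.** The point holds for the continuous outcomes measured at t0, t+2, t+4 and t+6. The stated analysis leaves the treatment test open between a diluted main effect and a 3-df interaction, and it discards partial follow-up.

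The dilution factors, 3/4 and 1/2, follow from the design once an effect profile is given. The power figures and the 43-36 complete cases rest on the assumptions listed above. If the interaction is read, the shortfall against ANCOVA at t+6 is material for a linear effect at low to moderate correlation (54% against about 80% at r = 0.4). For a constant effect it is smaller, and it is gone by r = 0.7. Repeated-measures ANOVA with a Group x Time test is a valid analysis of a randomised trial, so this is an improvement in efficiency and clarity and not the correction of an invalid test. It should be made because it is nearly free.

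**What to change.** For these continuous outcomes, replace the ANOVA with a linear mixed model:
- response: values at t+2, t+4 and t+6;
- fixed effects: baseline value, group, visit and group x visit;
- unstructured covariance within patient;
- all randomised patients with at least one follow-up value.

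Name the between-group difference at t+6, with its 95% CI, as the treatment estimate. The Mauchly pre-test and the switch of post-hoc method then fall away.

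The cost is analysis wording only: baseline values are already collected, and the model is available in SPSS. The change does not apply to the binary primary outcome, hospital days or survival. It still leaves out patients with no follow-up value, and it does not resolve truncation by death.
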